#### Control arm

The standard pre-operative education program consists of information about the perioperative period, but does not include information on long-term recovery. The admission process, details about the anesthesia process, surgical technique, complications, pain management, the direct post-operative recovery and rehabilitation during the first 6 weeks post-operative are addressed. During a 120-min multidisciplinary pre-operative class an anesthesiology assistant, physiotherapist, orthopedic nurse and orthopedic surgeon teach a 30-min module each. The information is summarized in a brochure for the patients. This education module currently is the standard care in Máxima Medical Center for all TKA patients.

### Outcome measurement

Outcome measures used at the different time points can be found in Fig. 2.

**Fig. 2 Fig2:**
[figure not shown]
Standard Protocol Items: Recommendation for Interventional Trials (SPIRIT) summary of study timing and activities

#### Primary outcome measure

The primary outcome measure is a Numeric Rating Scale (NRS) score for satisfaction with treatment result at 12 months’ follow-up. The NRS satisfaction score is a self-reported measure for patient satisfaction [45]. Patients are asked to answer the question: “How satisfied are you (in general) about the result of your knee operation?” on a scale ranging from 0 (very dissatisfied) to 10 (very satisfied) [45]. “Very satisfied with treatment result” is defined as an NRS satisfaction score of ≥ 8.

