### Sample size and power calculations

The calculation of the number of patients needed for this trial was based on the following assumptions. Specific pre-operative information can lead to more realistic patient expectations, which subsequently leads to a higher probability of fulfilled expectations [15]. Furthermore, patients who have fulfilled expectations are more often satisfied with the results of TKA [13, 14]. Therefore, we hypothesize that patients are more often (very) satisfied with treatment outcome 1 year post-operative. Based on more realistic expectations after improved pre-operative education on long-term recovery, previous work has shown that 50% of patients are very satisfied after TKA, 23% somewhat satisfied, 11% neutral, 9% somewhat dissatisfied, and 7% were very dissatisfied with the outcome [62]. In our calculation, we used a power of 80% (type II error of 20%) and an alpha of 0.05 (type I error). To increase the proportion of very satisfied patients in the knee population with 20% (from 50% of very satisfied patients to 70% very satisfied patients), 90 patients are required in each group (180 TKA patients in total). The final total sample size required is 204 knee patients, to accommodate a 15% potential dropout rate.

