### Statistical analysis

The primary analysis will be performed according to intention-to-treat principles following the original group allocation regardless of the intervention that they actually received. Missing data will be accounted for by a multiple imputation technique. A secondary per-protocol analysis will be performed, including only those patients who completed the treatment originally allocated. Reasons for cross-over will be explored. Distribution of all variables will be tested by the Shapiro-Wilk test. For the normally distributed variables, parametric tests will be used. For the variables that were not normally distributed non-parametric tests will be used.

The primary outcome will be analyzed by using logistic regression analyses (patient satisfaction with the 12 months’ results of TKA as dependent and intervention as independent variable), variables of which a priori are known to be associated with patient satisfaction, based on previous studies or based on a strong clinical rationale, will be considered as covariates in the primary analysis. These covariates are age, gender, BMI and baseline expectations as assessed by the HSS Knee Replacement Survey, anxiety, depression. The assumptions of constant variance and linear relationships will be assessed using scatter plots. Should any of these assumptions seriously fail, then transformation of the dependent or independent variable(s) (where applicable) will be used. The choice of which transformation (e.g., square root, logarithm) will be used based on the specific distribution of the residuals. Similar analyses will be performed for the secondary outcome parameters. Change in outcome expectations before and after pre-operative education (baseline vs pre-operative), and difference between intervention and control group in change in baseline and pre-operative expectations will be analyzed using linear regression analyses. Statistical calculations will be made using IBM® SPPS software, version 19.0.

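### The declared primary outcome is a 0–10 score, but the trial is powered and analysed on a dichotomy, with a 50% control rate from a different scale not shown to match NRS ≥ 8

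*Protocol article*

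**What the plan says.** Under Primary outcome measure the protocol says "The primary outcome measure is a Numeric Rating Scale (NRS) score for satisfaction with treatment result" at 12 months. The scale has 11 points, and only its upper end, 10, carries the label 'very satisfied'. The same paragraph adds that being very satisfied with the treatment result "is defined as an NRS satisfaction score of ≥ 8".

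Under Sample size and power calculations, planning rests on a proportion. Earlier work is cited in which "50% of patients are very satisfied after TKA, 23% somewhat satisfied, 11% neutral, 9% somewhat dissatisfied, and 7% were very dissatisfied with the outcome". The target is a rise "from 50% of very satisfied patients to 70% very satisfied patients", with 80% power and alpha 0.05, giving 90 per group, 180 in total, and 204 after an allowance for dropout.

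Under Statistical analysis, "The primary outcome will be analyzed by using logistic regression analyses", with patient satisfaction as the dependent variable and no cut stated. The covariates are age, gender, BMI, baseline expectations, anxiety and depression. Then follows: "The assumptions of constant variance and linear relationships will be assessed using scatter plots", with transformation of the dependent or independent variables if these fail. Under Randomization, allocation is stratified by orthopaedic surgeon; surgeon is not among the covariates.

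**The concern.** Three parts of the plan should describe one endpoint, and they do not quite do so. The outcome section names a score. The sample size and the model need a yes/no variable. The model checks suit a continuous one. NRS ≥ 8 has to be inferred as the primary endpoint, which leaves room to argue later over which variable was primary.

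The second difficulty is the planning rate. The 50% was observed for the top box of a verbal scale with five options. The trial will count patients who score 8, 9 or 10 on a numeric scale. If some patients who would have chosen 'somewhat satisfied' give an 8, the control rate exceeds 50%, and on the protocol's own figures it could reach 50% + 23% = 73%. The stated 80% power therefore depends on a match between two scales that the article does not examine.

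**Working it through.** **Inputs.** Control 50%, intervention 70%, power 80%, alpha 0.05, 90 per group and the verbal distribution 50/23/11/9/7% all come from Sample size and power calculations. The 1:1 allocation is from Study design. Two-sided testing is assumed because sidedness is not stated.

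**Reproducing the plan's figure.** With unpooled variance,

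n = [p₁(1−p₁) + p₂(1−p₂)] × (1.960 + 0.842)² / (p₂−p₁)² = (0.25 + 0.21) × 7.849 / 0.04 = 90.3 per group.

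The pooled-variance formula gives 93. The plan's 90 is reproduced.

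**Sensitivity to the control rate at NRS ≥ 8.** With pooled variance under the null, power = Φ{[(p₂−p₁)√n − 1.960√(2p̄(1−p̄))] / √[p₁(1−p₁)+p₂(1−p₂)]}. For 50% versus 70% and n = 90 this is Φ[(1.897 − 1.358)/0.678] = Φ(0.795) = 78.7%.

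The planned effect can be carried to another control rate in two ways: hold the odds ratio, (0.70/0.30)/(0.50/0.50) = 2.33, so that p₂ = 2.33p₁/(1 − p₁ + 2.33p₁); or hold the 20-point difference.

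| Control rate | Intervention rate, OR 2.33 | Power | Intervention rate, +20 points | Power |
|---|---|---|---|---|
| 40% | 60.9% | 80.5% | 60% | 77.0% |
| 50% | 70.0% | 78.7% | 70% | 78.7% |
| 60% | 77.8% | 73.5% | 80% | 83.9% |
| 70% | 84.5% | 64.2% | 90% | 92.5% |
| 73% | 86.3% | 60.4% | 93% | 95.3% |

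The upper limit of 73% is an assumption: all of the 'somewhat satisfied' group score 8 or more. The 40% row shows that an error in the other direction matters little.

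**What the cut discards.** Under proportional odds (Whitehead), power = Φ{√[n (ln OR)² f / 6] − 1.960}, with f = 1 − Σp̄ᵢ³, p̄ᵢ the mean of the two arms' category probabilities, and (ln 2.33)² = 0.718.

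- Dichotomy: f = 1 − (0.60³ + 0.40³) = 0.720; √(90 × 0.718 × 0.720/6) = 2.784; power 79.5%.
- Five verbal categories: f = 0.775; √(90 × 0.718 × 0.775/6) = 2.889; power 82.4%.

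The gain on the protocol's own figures is about 3 points. Spreading the top half over 8, 9 and 10 as 20/18/12% gives f = 0.967 and power of about 90%, but that spread is assumed; the article gives no NRS distribution.

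**When proportional odds fails.** These are simulations at 90 per group, using a rank test in place of the unadjusted ordinal model.

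- The whole 20-point gain comes from 'somewhat' moving to 'very satisfied' (23% to 3%, 50% to 70%): the cut has about 80% power and the ordinal test about 46–49%.
- The 27% neutral or dissatisfied (11 + 9 + 7) are halved into 'somewhat satisfied', all below the cut: the cut sees no effect, and the ordinal test has only about 13–14% power.

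**The case against.** The best defence is that the responder endpoint is recoverable. NRS ≥ 8 is defined in the paragraph that names the scale, it is the only binary definition in the article, the sample size uses the same term, and logistic regression requires such a variable. Powering on a pre-defined responder cut is legitimate, and the 90 per group is arithmetically sound. An article may also leave model detail to a fuller document. All of this stands, and it makes the first part a repair of wording. It does not remove the mismatch: what the article does state about the declared variable, the model checks and the planning rate does not fit together.

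Three stronger readings are tempting and are not supported.

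- *The trial is underpowered.* That holds only with the odds ratio fixed. The protocol expresses its target as a move from 50% to 70% and states no odds ratio; with the 20 points fixed, a higher control rate raises power.
- *The cut wastes substantial power, so the ordinal model should replace it.* The gain on the documented distribution is about 3 points, and it reverses if the benefit is concentrated at the top of the scale.
- *An ordinal test would rescue an effect confined to dissatisfied patients.* At about 13% power it would not. Nor does the cut ignore all improvement among dissatisfied patients: any move from below 8 to 8 or above counts.

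**Conclusion.** The point holds as an inconsistency and an unsupported planning input. The declared outcome is a score, the powered and analysed outcome is a dichotomy that must be inferred, and the constant-variance and transformation checks do not apply to it. The 50% comes from a different scale, so the 80% power is conditional on an undocumented match. Over control rates of 50–73% at 90 evaluable patients per group, power runs from about 79% down to 60% (odds ratio 2.33 held) or up to 95% (20-point gain held).

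These figures assume two-sided testing, no covariate adjustment, and that NRS ≥ 8 captures the whole verbal top box plus anything from none to all of the next category. The documents cannot say where in that range the truth lies, so the stated power is unverified; they do not show it to be wrong.

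**What to change.** - In Primary outcome measure and in Statistical analysis, name NRS ≥ 8 at 12 months as the single primary endpoint.
- For that endpoint, delete the constant-variance check and the option to transform the dependent variable. Linearity of continuous covariates on the logit scale can stay. Add surgeon, the stratification factor, to the model.
- Pre-specify an ordinal (proportional-odds) analysis of the full NRS score as key secondary, with odds ratios at separate cuts to check proportionality.
- In Sample size and power calculations, state that the 50% comes from a five-category verbal scale, and give the power range in both directions.

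The cost is revised wording and a registry update before unblinding, which the protocol places after the data analysis. No extra patients or data are needed. The drawback is one more analysis to interpret, whose power advantage exists only if the effect is roughly proportional across the scale.

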#### Patient characteristics

At baseline, patient characteristics will be obtained: age, gender, side affected, height, weight, education level, duration of complaints and radiological osteoarthritis severity scored according to the Kellgren and Lawrence grading system [46].

#### Secondary outcome measures

##### Hospital for Special Surgery (HSS) Knee Replacement Expectations Survey

Patient expectations will be evaluated by the Dutch version of the HSS Knee Replacement Survey [34]. Measurements will be obtained at baseline (after inclusion at the outpatient clinic, before pre-operative education), at admission for surgery (after the pre-operative education) and fulfillment of expectations 12 months post-operatively. The HSS Knee Replacement Expectations Survey is a 19-item, self-administered survey, measuring probability-based outcome expectations in the domains of pain, function, activities and psychological wellbeing [7, 15]. The survey is reliable, validated, and considered to be a high-quality expectation assessment instrument [7, 34, 47]. Patients will be asked how much improvement they expect for each item; the following response format will be used: “complete improvement or back to normal,” “a lot of improvement,” “a moderate amount of improvement,” “a little improvement” or “this expectation does not apply to me/I do not have this expectation” [15, 34]. The total score ranges from 0 to 76, which will be recoded on a 100-point scale, with a higher score representing higher expectations [15, 34].

To assess to what extent expectations have been fulfilled 12 months post-operatively, the expectation fulfillment version of the HSS Knee Replacement Expectations Survey will be used [12]. Unfortunately no evaluation of the measurement properties of this modification are available. The perceived actual outcome is scored with the same answer options and score calculation as used for pre-operative measurement [12].

##### Knee injury and Osteoarthritis Outcome Score – Physical Function Short Form (KOOS*-*PS)

The KOOS-PS Dutch version is a seven-item knee-specific questionnaire for measurement of the construct physical function. From 5-point Likert scale questions, a normalized score is calculated ranging from no difficulty (0) to extreme difficulty (100) [48]. The KOOS-PS has good reliability, validity and ability to detect change over time in knee osteoarthritis patients [48, 49].

##### Oxford Knee Score (OKS)

The Dutch version of the OKS is a 12-item patient-reported measure for assessment of pain and function after TKA. Each question consists of a 5-point Likert scale, leading to a total score ranging from a best functional score of 12 to the worst functional outcome score of 60 [50]. It is short, reproducible, valid and sensitive to clinically important changes [49, 50].

##### EQ-5D

The Dutch version of the EuroQol 5D-3 L (EQ-5D) is a self-reported questionnaire, measuring generic health status [51]. The EQ-5D comprises five questions scored on a 3-point Likert scale and a Visual Analogue Scale (EQ VAS) where the endpoints are labeled “Best imaginable health state” and “Worst imaginable health state.” From the five questions a sum score can be calculated: 1 represents the best possible health state and lower scores imply a lower health state [51]. The EQ-5D has good reliability and validity in knee osteoarthritis patients [52].

##### NRS pain

The NRS score for pain during activity and at rest (NRS pain) during the past week will be measured on an 11-point scale. A score of 0 represents “no pain” and a score of 10 represents “worst imaginable pain.” The NRS has good reliability and responsiveness [53].

##### Anchor question

At the follow-up 12 months post-operative a 7-point Likert scale anchor question will be scored for change in activities of daily living. The question “How has your general daily functioning changed since the operation on your knee?” can be responded to on a 7-point scale ranging from 1 (a lot worse) to 7 (very much improved).

##### Hospital Anxiety and Depression Scale (HADS)

The Dutch version of the HADS is a 14-item questionnaire for the measurement of anxiety and depressive symptoms [54, 55]. Seven items that relate to anxiety and seven items that relate to depression are rated on a 4-point scale. For both subscales, a sum score will be calculated ranging from 0 meaning no symptoms to 21 meaning severe symptoms.

##### The Pain Catastrophizing Scale (PCS)

The Dutch version of the PCS is a reliable and valid self-reported measure of catastrophizing [56]. Catastrophizing is defined as an exaggerated negative orientation toward noxious stimuli and is an important aspect of pain experience and coping [56]. The PCS consists of 13 5-point scale questions about thoughts and feelings on pain experience. Subscales for rumination, magnification and helplessness have been defined. A total score can be calculated ranging from 0 (no catastrophizing) to 52 (extreme catastrophizing).

##### Life Orientation Test-Revised (LOT-R)

The Dutch version of the LOT-R assesses the constructs dispositional optimism and pessimism and has satisfactory psychometric properties [57, 58]. This self-reported measure consists of 10 items. Three items (1, 4 and 10) assess optimism, three items (3, 7 and 9) assess pessimism, and four are filler items. Response categories range from “strongly agree” to “strongly disagree” on a 5-point Likert scale. Scores for the two subscales can be calculated and the total score is calculated by adding the optimism and the inverted pessimism score.

##### Functional Co-morbidity Index (FCI)

Co-morbidity is scored using the FCI. The index consists of a list of 18 diagnoses associated with declining function [59]. One point is assigned to each diagnosis, and the points are summarized, giving the patient a score of between 0 and 18 [59]. The FCI is considered a reliable and valid tool for assessment of co-morbidity in osteoarthritis patients [60].

##### Complications

At 1-year follow-up complications that have occurred will be scored as advised by the Knee Society [61]. This classification system allows structured reporting of occurrence and severity of 22 potential complications after TKA [61]. Adverse events are deemed unlikely due to the study design, occurrence will be monitored and reported.

### Sample size and power calculations

The calculation of the number of patients needed for this trial was based on the following assumptions. Specific pre-operative information can lead to more realistic patient expectations, which subsequently leads to a higher probability of fulfilled expectations [15]. Furthermore, patients who have fulfilled expectations are more often satisfied with the results of TKA [13, 14]. Therefore, we hypothesize that patients are more often (very) satisfied with treatment outcome 1 year post-operative. Based on more realistic expectations after improved pre-operative education on long-term recovery, previous work has shown that 50% of patients are very satisfied after TKA, 23% somewhat satisfied, 11% neutral, 9% somewhat dissatisfied, and 7% were very dissatisfied with the outcome [62]. In our calculation, we used a power of 80% (type II error of 20%) and an alpha of 0.05 (type I error). To increase the proportion of very satisfied patients in the knee population with 20% (from 50% of very satisfied patients to 70% very satisfied patients), 90 patients are required in each group (180 TKA patients in total). The final total sample size required is 204 knee patients, to accommodate a 15% potential dropout rate.

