## Methods

### Study design

The influence of Expectation modification in Knee arthroplasty on Satisfaction of PatiEnts, a randomized Controlled Trial (EKSPECT) study is a randomized, clinical superiority trial, with a parallel-group design and 1:1 allocation ratio. Patients will be randomized to group (a) usual education plus an additional module on realistic expectations for long-term recovery, or in group (b) usual education. Patients will be naïve to study objective and difference between study groups. Measurements will be performed blinded for group allocation at baseline, on day of admission and 12 months after TKA procedure. A flow chart of the study procedures can be found in Fig. 1. The study has been reviewed and approved by the Máxima Medical Center Medical Ethics Committee (registration code NL54671.015.15). The study has been registered in the Dutch Trial Registry (registration number NTR5779) and has not been amended. If protocol amendments are conducted, these will be updated on the Trial Registry record. A Standard Protocol Items: Recommendations for Interventional Trials (SPIRIT) Checklist on the study protocol is provided as Additional file 1.

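### The enrolment target of 204 covers about 12% dropout, not the stated 15%; the cost is about 1.5 points of power

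*Protocol article*

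**What the plan says.** All the sample-size figures are in the protocol article, section Sample size and power calculations. The error rates are set in the words "we used a power of 80% (type II error of 20%) and an alpha of 0.05 (type I error"; the article does not say whether alpha is one- or two-sided. The target effect is a rise in the proportion very satisfied, "from 50% of very satisfied patients to 70% very satisfied patients". From these the article concludes that "90 patients are required in each group (180 TKA patients in total". It then gives the enrolment target: "The final total sample size required is 204 knee patients, to accommodate a 15% potential dropout rate". The Study design section fixes "with a parallel-group design and 1:1 allocation ratio", so 204 means 102 per group.

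The Statistical analysis section plans an intention-to-treat primary analysis by logistic regression, with age, gender, BMI, baseline expectations, anxiety and depression as covariates, and with multiple imputation for missing data.

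**The concern.** Three linked figures are given: 180 patients needed, 15% dropout, 204 enrolled. Any two of them determine the third, and the three do not agree. Neither usual inflation method leads from 180 and 15% to 204.

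What is at stake is how attrition and a null result will be read. A trial that lost between 12% and 15% of its patients would be reported as within its allowance, although it would have fallen below its own required 180. A reader weighing a null result would also credit the design with 80% power at a dropout level for which it was not sized.

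**Working it through.** **Inputs.** From Sample size and power calculations: p₁ = 0.50, p₂ = 0.70, alpha 0.05, power 80%, 90 per group, 15% dropout, 204 enrolled. From Study design: 1:1 allocation. Assumption: alpha is two-sided. One-sided testing gives 74 per group (pooled formula) or 83 (with continuity correction), and neither reproduces 90.

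**Step 1: reproduce the 90 per group.** Unpooled normal approximation:

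n = (1.960 + 0.842)² × [0.50 × 0.50 + 0.70 × 0.30] / 0.20² = 7.849 × 0.46 / 0.04 = 90.26.

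This gives the article's 90, rounded down.

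**Step 2: try to reproduce 204.**

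| Calculation | Result |
|---|---|
| Correct inflation, 180 / (1 − 0.15) | 211.8, so 212 (106 per group) |
| Common shortcut, 180 × 1.15 | 207 |
| Article's target | 204 |

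The article's figure is 8 below the correct one and 3 below the shortcut.

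**Step 3: what 204 delivers.**

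- Remaining after 15% dropout: 204 × 0.85 = 173.4, or 86.7 per group. Shortfall against 180: 6.6.
- Dropout that 204 does cover: 1 − 180/204 = 24/204 = 11.8%.
- Inflation actually applied: 204/180 − 1 = 13.3%.

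**Step 4: power for 50% versus 70%, unadjusted comparison of completers.** With d = 0.20:

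- Unpooled: Φ( d / √(0.46/n) − 1.960 ). At n = 86.7 this is Φ(2.746 − 1.960) = Φ(0.786) = 78.4%.
- Pooled: Φ( [d − 1.960 × √(2 × 0.6 × 0.4 / n)] / √(0.46/n) ).

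| Analysable per group | Unpooled | Pooled |
|---|---|---|
| 86.7 (204 with 15% lost) | 78.4% | 77.1% |
| 90 (the stated requirement) | 79.9% | 78.7% |
| 102 (204, none lost) | 84.6% | 83.5% |

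Within either column, going from 90 to 86.7 per group costs about 1.5 points. Exact enumeration of the uncorrected chi-square test gives 79.3% at 90 per group, 78.2% at 87 per group and 76.3% with 86 controls and 87 intervention patients. Exact power jumps between adjacent sample sizes because the outcome is discrete, so these values support the general level but not a finer figure.

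**The case against.** The strongest reply is that the planned primary analysis does not discard dropouts. It keeps all randomised patients through multiple imputation and adjusts for baseline covariates, so power computed on completers describes a different analysis. That stands in part: the power figures above are approximate, and the effect of adjustment and imputation cannot be quantified from the article. It does not rescue 204. The sample-size section itself defines the requirement as 180 plus a dropout allowance, and imputation does not restore all the information in a missing 12-month outcome.

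A second reply is that 8 patients in 212 (3.8%) and 1.5 points of power are small beside the uncertainty in the 50%, 70% and 15% inputs. That stands, and it is why the point is minor.

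A reader might go further and infer that the trial lacks its stated 80% power by about 3 points. That sets 77.1% from the pooled formula against an 80% obtained with the unpooled one. About half of that gap is the change of formula, since the pooled formula already gives 78.7% at the planned 90. A reader might likewise infer that the base of 90 is wrong because the pooled formula gives 93 per group, hence 219 enrolled. The article does not name its formula, the unpooled one is a legitimate choice that gives 90.26, and rounding down leaves 79.9%. Preferring 93 is a choice of method and shows no error in the plan.

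**Conclusion.** The stated dropout allowance is wrong as written: 204 enrolled patients allow for 11.8% dropout, and 15% would leave about 173 analysable against a required 180. This part is arithmetic on the article's own figures and needs no assumption.

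At 15% dropout, power is about 77–78%, of which the dropout slip accounts for about 1.5 points. This part assumes a two-sided alpha of 0.05 and an unadjusted comparison of completers. The shortfall arises only as dropout passes 11.8%; with every outcome observed, 204 gives about 84–85%. The document therefore does not support calling the trial materially underpowered. No endpoint, error rate or analysis changes. Severity: minor, but a definite error in a stated figure.

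**What to change.** Replace the final sentence of Sample size and power calculations with wording to this effect: 204 enrolled patients allow for about 12% dropout from the required 180; at 15% dropout about 173 would be analysable, with power of about 77–78% for 50% versus 70% (two-sided alpha 0.05, unadjusted comparison of completers). The sponsor should confirm that alpha is two-sided when making the change.

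The cost is one sentence, no additional patients, and a stated power about 2 to 3 points below 80% at 15% dropout. If the sponsor would rather keep the 15% allowance on its base of 180, the matching target is 212, which is 8 more patients.
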